# Costs according to DBC (Zorgautoriteit 2011)

‡ According to tariff of the Royal Dutch Society of Pharmacy

§ Indirect costs for paid work was calculated for each injured separately based on mean income of the Dutch population according to age and sex

^ According to cost research on self-reference to GP and ER [22]

Besides the cost of the intervention itself, direct health care costs were included: i.e. costs of care by a general practitioner, physiotherapist, massage therapist, alternative therapist, and care by a sports physician or other medical specialist (e.g., orthopaedic surgeon, general surgeon); hospital care; use of drugs (e.g., paracetamol/actaminophen, ibuprofen) and medical devices (e.g., crutches, tape, braces). The costs of drugs were estimated on the basis of prices recommended by the Royal Dutch Society of Pharmacy [19]. Also indirect costs resulting from a loss of production due to absenteeism from paid or unpaid work were included. Indirect costs for absenteeism from paid work were calculated using the friction cost approach of 4 months, based on the mean age and sex-specific income of the Dutch population [18,20]. Indirect costs for productivity loss of unpaid work, such as study and household work, costs were estimated at a shadow price of €7.94 an hour [18].

### Process evaluation

A process evaluation was conducted for the three interventions. A supplement questionnaire was added to the monthly questionnaire after the intervention: for the neuromuscular training group after 2 months; for the brace group after 2 months and after 1 year; and for the combined group 2 questionnaires: one for evaluation of the training and one for evaluation of the brace, both added after 2 months. The questionnaire contained questions on the subjective response to the program (e.g. attitude towards neuromuscular training and braces), the presentation of the interventions, the perceived effect of the interventions, the support from peers for the participation in the program and questions on motivation for, and-compliance to the program.

### Statistical analyses

To evaluate the success of the randomisation, baseline values were analysed for differences between intervention group and control group, using a chi-square for categorical data and a student's t-test for numerical data.

All analyses were carried out according to the intention-to-treat principle. Cox-regression analysis was used to compare ankle recurrence risk between the intervention groups, using a significance level of P < 0.05. Other variables were checked for confounding and/or effect-modification and were adjusted for accordingly. Absence from sports was tested between groups using a Mann-Whitney test, since absence from sports due to an injury is not normally distributed [11].

Mean direct, indirect and total costs were estimated and compared between the three groups, both for the costs per subject in the injured population and for the costs per subject in the total population. Because costs are not normally distributed, 95% confidence intervals for the differences in mean costs were obtained by bias corrected and accelerated bootstrapping (2000 replications) [21]. Differences in costs and differences in ankle sprain recurrences were compared against the cheapest intervention (neuromuscular training) in a cost-effectiveness ratio, which estimated for each other condition the additional cost to prevent one ankle sprain recurrence. Confidence intervals for the cost-effectiveness ratio were calculated with bootstrapping, using the bias-corrected percentile method with 5000 replications. Uncertainty regarding the estimate of this ratio was expressed on a cost-effectiveness plane.

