### Recruitment of study population

Participants were recruited through the internet. Information on the study and a call for participation were available on the website: http://www.anklesbackincontrol.nl. The study was supported by the Dutch Association for Sports and Exercise Medicine (VSG), the Royal Dutch Physiotherapy Association (KNGF), the Dutch Orthopedic Association (NOV) and the Dutch College of General Practitioners (NHG). The participating organizations placed a hyperlink on their website. Hereby, individuals seeking medical information regarding ankle sprains in any of these sites came across this call for participants. Similar calls were placed on the websites of sporting associations of sports with a relatively high ankle sprain rate (e.g. soccer, volleyball, handball, basketball, korfball and tennis). Where possible existing electronic newsletters of sporting associations were used to contact potential participants directly. Next to the mentioned calls for participation on websites, we recruited actively by placing calls for participation on sports-related internet fora, as well as by electronic newsletters. This method of recruitment resulted in a sample of participants from a wide spectrum of different activities, sports and ages. Thus we created a sample representative to the Dutch sporting population. A similar recruitment strategy was successfully employed in a previous study on the same topic [15].

Recruitment of participants for the ABrCt study took place between April 2010 and May 2011. A total of 450 people were interested to participate in the ABrCt study and reacted on the call for subjects with a recent ankle sprain. A total of 18 athletes were classified as non-responders after a maximum of ten attempts to contact them through telephone or email failed. Of 432 people who were available for inclusion, 48 were excluded. Reasons for exclusion were: no return of baseline questionnaire (3), still undergoing treatment at the end of the inclusion period (5), no agreement on informed consent (2), vestibular complaints (2), non-recent ankle sprain (injury > 2 months before inclusion) (25), other serious injury (e.g. fracture of the ankle) (5) and private reasons (6). After completion of the baseline questionnaire and informed consent, 384 athletes were randomly assigned to the neuromuscular training group (n = 122), brace group (n = 126), and combined group (n = 136).

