### Randomization procedure

After subjects had finished ankle sprain treatment by means of usual care, they were randomized to any of the three study groups. Stratification was based on type of usual care; (para-)medical treatment or no treatment/other treatment. Randomization took place at the end of usual care in order to minimize the chance of alterations in the treatment due to prior knowledge of the allocated intervention. As an example, a caregiver might decrease the amount of strengthening exercises when a patient was allocated to the neuromuscular training group. Even so, the other way around a caregiver might feel obliged to include additional strength and balance exercises when a patient is allocated to the brace group. Therefore, participants were asked to follow their usual treatment and/or rehabilitation program and received the allocated secondary preventive intervention after usual care had finished (and ideally before sports participation commenced).

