### Baseline measurement

When a potential participant responded to one of our calls, he or she was contacted by phone. During this initial contact the background and proceedings of the proposed study were explained by protocol. When the potential participant agreed to partake in this study an informed consent was sent by ordinary mail which he or she was required to sign and return by ordinary mail within one week. In addition, an e-mail was sent containing a hyperlink to the baseline questionnaire, which he or she was required to complete within one week. This baseline questionnaire gathered information of each participant on demographic variables, physical characteristics, sports & injury history, use of preventive measures, details and injury mechanisms of the current ankle sprain, and subsequent treatment and/or rehabilitation.

In order to create similar groups with respect to the outcome measures, participants were stratified by treatment, i.e. (para-)medical treatment or other/no treatment. As gender has never been identified as a factor related to secondary ankle sprain complaints, this was not a parameter for stratification. The participant was randomized to any of the three study groups and received oral and written instructions for the specific group allocation directly after completion of usual care.

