### Co-intervention

Two Dutch medical guidelines explicitly describe the use of neuromuscular training and sports braces for the treatment of acute lateral ankle sprains. These are the guidelines of the Royal Dutch Physiotherapy Association (KNGF) and of the Dutch Association of Sports and Exercise Medicine (VSG). In the KNGF guideline neuromuscular training is mentioned as part of the primary treatment from 11 days to 12 weeks after sustaining an ankle sprain. Only in case of functional ankle instability neuromuscular training (on a balance board) is advised explicitly. A brace is advised in case of insufficient neuromuscular control. It is repeatedly advised to decrease brace use as soon as possible. Furthermore athletes are advised not to wear a brace during training, but only during matches. In the VSG guideline neuromuscular training is advised from day 5 after sustaining an ankle sprain (grade 1). The use of a brace after sport resumption is advised during 3 to 6 weeks depending on the severity of the sprain.

Taking into account the ruling KNGF and VSG guidelines, co-interventions through inclusion of similar interventions in the regular treatment protocol could have been possible. By registering the content of the provided care for the initial ankle sprain, for which participants were included in the study, we are able to correct for co-interventions. Nevertheless, the aim of this study was to evaluate the added value of neuromuscular training and brace use during sports on top of usual care as advised in these guidelines.

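### The primary Cox comparison is left to data-dependent adjustment, with no guarantee that the stratification factor is in the model

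*Protocol article*

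**What the plan says.** Four places in the protocol article bear on this point.

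- **Statistical analyses, primary comparison:** "Cox-regression analysis was used to compare ankle recurrence risk between the intervention groups, using a significance level of P < 0.05". The next sentence gives the rule for covariates: "Other variables were checked for confounding and/or effect-modification and were adjusted for accordingly".
- **Randomization procedure:** "Stratification was based on type of usual care; (para-)medical treatment or no treatment/other treatment". The Baseline measurement section gives the reason: "In order to create similar groups with respect to the outcome measures, participants were stratified by treatment".
- **Co-intervention, in the Discussion:** because the care received for the index sprain was recorded, the article holds that adjustment for co-interventions is possible. This describes a possibility and is not tied to a particular model.
- **Statistical analyses, baseline:** to judge whether randomisation succeeded, "baseline values were analysed for differences between intervention group and control group, using a chi-square for categorical data and a student's t-test for numerical data".

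**The concern.** The covariate rule is stated text, not a gap. It says that the model was settled by checking variables, without saying which variables, by what criterion, or which fitted model carries the primary result. Three things follow.

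- The investigators expected type of usual care to be related to outcome, which is why they stratified on it. Under the rule as written it enters the Cox model only if a check selects it. A factor balanced by design belongs in the model by design.
- Hazard ratios are not collapsible: adding a prognostic covariate changes the quantity estimated even when the arms are perfectly balanced. Choosing covariates from the data therefore affects what the primary hazard ratio means, as well as its precision.
- Confounding and effect modification share one sentence and one remedy. Acting on an effect modifier means adding an interaction, after which the arm term is no longer the overall effect. Nothing marks such a result as exploratory.

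At stake is whether the primary hazard ratio and its P value come from a model fixed by the design or from one chosen among several after the fact.

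**Working it through.** **1. Where the stratification factor appears.** Type of usual care (two levels) is in Randomization procedure and again in Baseline measurement. Statistical analyses does not name it, either as included or as excluded. The only route into the model that the text describes is the check on other variables.

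**2. How open the rule is.** The article gives no list, threshold or primary model. Baseline measurement describes a questionnaire covering six domains: demographics, physical characteristics, sports and injury history, preventive measures, details of the current sprain, and its treatment or rehabilitation. The pool of candidates is therefore not small.

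**3. Type I error.** The plan states no figure on this point, and the documents give no event rate or covariate effects, so these inputs are assumed. Arm size is 356/3 = 118.7, taken as 119. Both simulations compare two arms with no true effect at nominal 5%.

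*Simulation A:* 20% recurrence, 10 covariates of which 4 are prognostic (HR 1.5 per SD), 600 runs.

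| Analysis | Type I error |
|---|---|
| Unadjusted | 4.5% |
| 10% change-in-estimate selection | 4.7% |
| Pre-specified covariates | 4.5% |
| Significant in either of the first two | 6.0% |

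The Monte Carlo standard error of the last line is sqrt(0.06 × 0.94/600) = 0.0097, so 6.0% lies about one standard error above 5% and cannot be told apart from it.

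*Simulation B:* about 30% recurrence, usual care balanced by stratification with log-HR 0.5, 6 or 10 candidate covariates of which half are prognostic (log-HR 0.3), 1,500 runs.

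| Analysis | 6 candidates | 10 candidates |
|---|---|---|
| Unadjusted | 4.0% | 4.7% |
| Stratification factor in the model | 4.7% | 4.7% |
| 10% change-in-estimate selection | 4.7% | 5.5% |
| Most favourable of unadjusted, single-covariate and full models | 7.3% | 8.4% |

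At 5% the standard error is sqrt(0.05 × 0.95/1500) = 0.0056. The mechanical rule is within one standard error of 5%. The last row is about 4 and 6 standard errors above it: (0.073 − 0.050)/0.0056 = 4.1 and (0.084 − 0.050)/0.0056 = 6.1. Omitting the stratification factor did not inflate the error.

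**4. False interactions.** If k independent variables are each tested as effect modifiers at 5%, the chance of at least one false positive is 1 − 0.95^k:

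- k = 3: 14.3%
- k = 5: 22.6%
- k = 6: 26.5%
- k = 10: 40.1%

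The counts, the independence and the 5% criterion are all assumed; the article gives none of them.

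**5. Baseline comparison.** Recruitment of study population reports 122 + 126 + 136 = 384 athletes randomised to training, brace and combined arms. All three are active, so there is no control group. A two-sample t-test of an intervention group against a control group cannot be applied to this design as written. Under proper randomisation any baseline difference is chance, so a significance test does not show whether randomisation worked.

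**6. Sample size.** Fixing the model in advance does not alter the stated 99 per group or 356 in total, which rest on a cost difference.

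**The case against.** The strongest reply is that this is a condensed article and that a full protocol or analysis plan may fix the covariates. Three stronger readings that a reader might infer fail for this or a similar reason.

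- **That the Cox model leaves out the stratification factor.** The article does not say so. Type of usual care could be among the other variables or be specified elsewhere, and the Co-intervention section shows that adjustment for prior care was at least contemplated. Only the absence of a guarantee can be claimed.
- **That the baseline tests decide which covariates enter.** The article gives those tests a single purpose, judging the randomisation, and describes the confounder check in a separate paragraph that does not refer to them.
- **That the false-positive risk of the primary comparison is 23% or 40%.** Those are chances of at least one spurious interaction under assumed counts, not type I error for the arm comparison. Nor does the article say that the most favourable model would be chosen, which is what the 7.3% to 8.4% assumes.

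These limits stand. The reply does not remove the point, because the article does more than stay silent on covariates: it states a data-dependent rule for the primary analysis. The control-group wording is a genuine inconsistency, but it touches only the baseline description. The same section compares recurrence between the intervention groups and costs between the three groups.

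**Conclusion.** The point holds in limited form. The stated rule lets the data decide which unnamed variables enter the primary Cox comparison as confounders or effect modifiers, and it does not guarantee that type of usual care is in the model. The primary hazard ratio can therefore depend on choices made after the data are seen, and a chance interaction could be given the same standing as the overall effect.

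No size can be derived from the documents. Under the assumed inputs, a mechanical selection rule produced almost no inflation and free choice among models moved 5% to roughly 7% or 8%. The article does not bind the analyst to a mechanical rule, but it does not describe free choice either. This does not invalidate the trial; it is an improvement that should be made because it costs almost nothing. The mismatch between the baseline tests and the three active arms is certain from the text, but secondary.

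**What to change.** State one primary analysis: a Cox model of the three arms, stratified by or adjusted for type of usual care. Add at most a short list of baseline covariates, chosen from items that the questionnaire actually collected and fixed before outcomes are examined. The article mentions sports and injury history only in general terms, so the availability of any specific item should be confirmed first. If outcomes have already been examined, the model with the stratification factor alone can still be justified, because the design determines it. Label every other adjustment and every effect-modification check as exploratory, and report the overall arm effects whatever those checks show.

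Replace the baseline significance tests with a table describing the three arms side by side, and remove the reference to a control group.

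The cost is a few sentences and one model term. The sample size is unchanged and no new data are needed.

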### Outcome measures

The primary outcome measure was incidence of ankle sprain recurrences, presented as the number of ankle sprain recurrences per 1,000 hours of sports participation. The following generic injury definition was used in this study: "An ankle sprain occurring as a result of sports participation or other daily activities and which causes one or more of the following:

• the subject has to stop the sports activity; and/or

• cannot (fully) participate in the next planned sports activity; and/or

• cannot go to work/school the next day; and/or

• needs medical attention (ranging from onsite care by e.g. first aid personnel, to personal care by e.g. physiotherapist, ER-doctor, or sports physician)."

Secondary outcome measures included the direct and indirect costs of recurrent injury, the severity of recurrent injury, and the residual complaints during and after the intervention.

This study has a one-year follow-up with measurements scheduled monthly for 12 months after baseline. All questionnaires and other forms were web-based and an invitation to fill out the questionnaires was sent to athletes by e-mail (with hyperlink), unless requested otherwise by the participant.

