### Injury registration

When a participant sustained an ankle injury during the follow-up period, the participant acknowledged this by e-mail. As a fail safe, ankle sprain recurrences were also recorded through the monthly follow-up questionnaire. After an injury was registered, the participant received an injury registration form. This form contained detailed questions on the diagnosis, the cause, and the aetiology of the re-injury. Furthermore, the advised treatment and the person who treated the injury were registered. The same form has been previously employed successfully in ankle sprain prevention studies [11,15]. Based on this form, a cost diary was sent to the athlete.

To evaluate the cost-effectiveness of the different intervention interventions participants who sustained an ankle sprain received a cost-diary.

The cost-diary is a log, which registered all absence from work, school and other chores of life, and (para-)medical treatment (including use of medication) from the moment of injury onwards until full recovery. From these cost-diaries direct and indirect costs resulting from the sustained ankle sprain could be calculated for use in an economic evaluation.

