### Cost-effectiveness evaluation

The aim of the economic evaluation was to determine and compare the total costs for subjects in all three trial arms, and to relate these costs to the effects of these groups.

The economic evaluation was performed from a societal perspective. Table 3 provides an overview of the costs collected [18,19]. Cost of the intervention included costs that were directly related to the implementation of the intervention programmes. These costs included for the neuromuscular training program, the written information materials, an instructional video, development and maintenance of an informational website, and the balance boards. For the brace group only the costs of the brace and maintenance of an informational website were taken into account.

**Table 3 T3:** Costs as applied in the economic evaluation

Costs	Cost (€)
Direct health care costs:	
General practitioner (mean cost of total visits)^	87.19
Physical therapist (per visit = 30 min)*	28.00
Sports physician (per visit = 30 min)*	80.00
Medical specialist (mean cost of total visits)#	89.24
Hospital costs (if seen by specialist)#	397.80
Alternative therapist (per visit)*	27.20
Emergency room (per visit) ^	197.12
Drugs‡	n.a.
Medical devices‡	
Tape (per roll)	4.00
Brace	79.50
Crutches (rent per week)	15.00
Indirect costs:	
Absenteeism from paid work (per day)§	n.a.
Absenteeism from unpaid work (per hour)*	7.94

€ 1.00 = $ 1.47 = £ 0.89 (d.d. 07-06-11)

* Costs according to Dutch guidelines

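### The between-arm cost comparison in the injured population conditions on the primary outcome, is not intention-to-treat, and should be descriptive beside the planned total-population comparison

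*Protocol article*

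**What the plan says.** All references are to the protocol article.

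- **Cost comparison (Statistical analyses).** Mean direct, indirect and total costs are compared between the three groups "both for the costs per subject in the injured population and for the costs per subject in the total population". Bias-corrected and accelerated bootstrap 95% confidence intervals are planned for the differences in mean costs. They are not limited to one population, and neither comparison is called primary or descriptive.
- **Analysis principle (Statistical analyses).** "All analyses were carried out according to the intention-to-treat principle".
- **What defines the injured (Outcome measures).** "The primary outcome measure was incidence of ankle sprain recurrences". Severity of recurrent injury is a secondary outcome.
- **Who supplies injury costs (Injury registration).** "participants who sustained an ankle sprain received a cost-diary".
- **Economic aim (Cost-effectiveness evaluation).** The aim is to "determine and compare the total costs for subjects in all three trial arms, and to relate these costs to the effects of these groups". Intervention costs are part of the evaluation.
- **Absence from sport (Statistical analyses).** "Absence from sports was tested between groups using a Mann-Whitney test, since absence from sports due to an injury is not normally distributed". Whether participants without a recurrence enter this test with zero days is not stated.

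**The concern.** Recurrence is the event the interventions are meant to prevent. Restricting a between-arm comparison to those who had it selects a subset of each arm by a consequence of treatment. If the arms differ in how many or which sprains they prevent, the injured subsets are no longer comparable, and a difference in their mean costs mixes treatment effect with selection. A blanket intention-to-treat statement cannot cover that contrast.

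What is at stake is how the economic results are read. Two cost differences will appear side by side, each with an interval and neither marked as the one to rely on. An arm that prevents mild sprains keeps a costlier residue and can look worse per injured participant. An arm that prevents all severities equally can look no better per injured participant despite a real saving. The Impact of results section says the findings could change clinical guidelines.

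**Working it through.** The article states no figure for this point. The check is an expected-value calculation on **assumed** inputs, since no recurrence rate or severity mix is given. Each injured participant is taken to have one recurrence.

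**Formulas.** Let m and s be the proportions with a mild or severe recurrence, c_m and c_s their costs, and K the intervention cost per participant.

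- Injury cost per injured = (m·c_m + s·c_s) / (m + s)
- Injury cost per randomised = m·c_m + s·c_s
- Either one including intervention cost = the above + K

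The injured-only figure drops the recurrence proportion (m + s), which is where a preventive effect appears.

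**1. Proportional prevention.** c_m = €50, c_s = €300. Arm A: m = 0.20, s = 0.10. Arm B: both halved.

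- Per injured: A = (10 + 30)/0.30 = €133; B = (5 + 15)/0.15 = €133.
- Per randomised: A = €40; B = €20.

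The benefit is hidden, not reversed.

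**2. Only mild recurrences prevented.** 100 participants per arm, c_m = €50, c_s = €600. A has 20 mild and 10 severe recurrences; B has 5 mild and 10 severe.

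- Per injured: A = 7000/30 = €233; B = 6250/15 = €417.
- Per randomised: A = 7000/100 = €70.0; B = 6250/100 = €62.5.

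The two differences have opposite signs.

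**3. Range.** A fixed at 20% mild and 10% severe; B prevents a share of the mild ones only. Differences are B minus A, in euros, without intervention cost.

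| c_m / c_s | Mild share prevented | Per injured | Per randomised |
|---|---|---|---|
| 50 / 300 | 25 / 50 / 75 / 100% | +17 / +42 / +83 / +167 | −2.5 / −5.0 / −7.5 / −10.0 |
| 50 / 600 | 25 / 50 / 75 / 100% | +37 / +92 / +183 / +367 | −2.5 / −5.0 / −7.5 / −10.0 |
| 100 / 300 | 25 / 50 / 75 / 100% | +13 / +33 / +67 / +133 | −5 / −10 / −15 / −20 |

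Under this mechanism the signs differ in every row.

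**4. Adding intervention cost.** The Sample size section puts training at €25 and a brace at €50. Take step 2 with A as training (the reference in the cost-effectiveness ratio) and B as brace.

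- Per randomised: 70 + 25 = €95 against 62.5 + 50 = €112.5.
- Per injured: 233 + 25 = €258 against 417 + 50 = €467.

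Both now point the same way, so the reversal of total cost is gone. The largest saving per randomised participant in step 3 (€20) is also below the €25 gap in intervention cost. If instead the more protective arm is the cheaper one (A brace, B training), the figures are 70 + 50 = €120 against 62.5 + 25 = €87.5 per randomised, and 233 + 50 = €283 against 417 + 25 = €442 per injured, so the reversal returns. It can also occur for indirect costs, which contain no intervention cost.

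**5. Absence from sport, if the test were restricted to the injured.** A simulation used 119 per arm, the recurrence proportions of step 3, and assumed lognormal days lost with medians 4 (mild) and 25 (severe). An injured-only Mann-Whitney test called the more protective arm significantly worse in about 17% of trials when half the mild recurrences were prevented and about 46% when three quarters were, against about 2% with no effect. These figures assume both the restriction and the selective mechanism.

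**The case against.** **The randomised contrast is already planned.** This stands. A reader might infer that costs are compared among re-injured participants only; the sentence quoted above names the total population too. The stated economic aim concerns all three arms, and additional cost per recurrence prevented makes sense only over everyone randomised, although the ratio's population is not named. The economic conclusion therefore need not rest on the injured-only figures. That does not justify giving those figures inferential intervals under an intention-to-treat label.

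**Reversal is not shown for total cost.** This also stands. A reader might infer that the plan will reverse the direction of the cost effect. With the article's own intervention costs and training as reference, the illustrated reversal disappears. Nothing in the article suggests that mild sprains are selectively prevented, and the first hypothesis expects the same 50% reduction in each arm. Still, the trial exists to compare the arms, so its analysis should not depend on their being alike.

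**Absence from sport.** A reader might infer that the Mann-Whitney test is confined to the injured. The phrase about absence due to an injury makes that plausible, but the population is not given, and a condensed article may leave it to the analysis plan. Nor must the test be replaced: the named outcome is severity of recurrent injury, whereas days lost per randomised participant measures total burden and combines frequency with severity.

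**Conclusion.** The point holds for the injured-only cost comparison. It is explicitly planned, is conditioned on the post-randomisation primary outcome, carries confidence intervals without being marked as subordinate, and conflicts with the statement that every analysis is intention-to-treat.

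How far it misleads cannot be fixed from the article. Under assumed inputs it can hide a halving of injury cost per randomised participant, or differ in sign from the randomised difference in injury-related or indirect costs. Reversal requires the severity mix to shift between arms. For total cost it also requires that the injury saving is not outweighed by a higher intervention cost. If the arms share the same recurrence rate and severity mix, the injured-only contrast does no harm.

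The article does not support a claim that the randomised cost comparison is missing, that total-cost conclusions will reverse, or that the absence-from-sport test is in fact restricted to the injured.

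**What to change.** 1. Make the between-arm difference in mean cost per randomised participant the sole inferential cost comparison, with intervention cost included and zero injury cost for those without a recurrence. Keep the planned bootstrap intervals for it.
2. Report direct, indirect and total costs among the injured descriptively per arm, without between-arm confidence intervals or tests, and state that this group is defined after randomisation.
3. If the absence-from-sport test is restricted to re-injured participants, label it a conditional, non-randomised description of severity. Days lost per randomised participant may be added as a supplementary analysis of total burden; it does not replace the severity outcome.

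The cost is wording only, with no new data. The downside is that the per-injury cost contrast loses its inferential status.
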